### Inclusion criteria

2.3

The study will include participants who satisfy all of the following inclusion criteria:
Diagnosis of chronic heart failure in a stable condition (defined as no acute decompensation, and no hospitalization for heart failure within at least 2 weeks before randomization), classified as heart failure with mildly reduced ejection fraction (LVEF: 41%–49%) or heart failure with preserved ejection fraction (LVEF≥50%), with BNP ≥35 pg/mL, and at least one of the following echocardiographic features present: left ventricular hypertrophy and/or left atrial enlargement; diastolic dysfunction, according to the 2018 Chinese Guidelines for the Diagnosis and Treatment of Heart Failure, and meeting the criteria of “Qi deficiency, blood stasis, and water stasis” syndrome;Patients must be on stable guideline-directed medical therapy for heart failure prior to randomization, defined as no major changes in medications within at least 2 weeks;NYHA classification of II to III;Age between 18 and 80 years;Voluntary acceptance the medication treatment and provision of an informed consent form trained investigators.

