### Follow-up visits and monitoring schedule

2.8

The study will start with a 7-day preliminary phase where eligible individuals will provide their consent and initial information will be gathered. Future appointments will be planned for 6 days ± 1 day (visit 1), 4 weeks ± 3 days (visit 2), and 12 weeks ± 3 days (visit 3) after starting the treatment. Follow-up assessments will be conducted at Week 12 ± 7 days post-discontinuation of treatment (24W ± 7d) (visit 4). To minimize loss to follow-up, participants will be regularly contacted through telephone calls and WeChat group communication. Reminders will be provided before each scheduled visit to improve retention and adherence. Table 1 outlines the comprehensive assessment timetable.

**Table 1 T1:** Schedule of enrollment, interventions, and assessments.

Study phase time	Lead-in period	Treatment period			Follow-up period
	Screening (−7D-0D)	Baseline (6D ± 1d)	Week 4 (4W ± 3d)	Week 12 (12W ± 3d)	Week 24 (24W ± 7D)^a^
Patients					
Eligibility screen	X				
Inclusion/exclusion criteria	X				
Informed consent	X				
General information	X				
Medical history	X				
Allocation	X				
Pregnancy examination	X				
Outcomes					
Primary outcome					
6-minute walk test	X	X	X	X	X^c^
Secondary outcomes					
BNP	X	X	X	X	X
MACE (including cardiac death, non-fatal myocardial infarction, and rehospitalization due to heart failure) ^b^	X	X	X	X	X
NYHA classification	X	X	X	X	X
KCCQ quality of life score	X	X	X	X	X
Exploratory outcomes					
Diuretic usage		X	X	X	X
Echocardiography	X			X	X
Heart failure-related rehospitalization rate^b^	X	X	X	X	X
TCM syndrome score	X	X	X	X	X
Myocardial enzyme levels	X			X	X
Inflammatory markers and other biochemical indicators	X			X	X
Safety					
Vital signs	X	X	X	X	X
Biochemical indexes	X			X	X
Electrocardiogram results	X			X	X
Adverse events	X	X	X	X	X
Others					
Drug distribution	X		X		
Drug recycle			X	X	
Combined medication			X	X	
Confirmation of medication compliance		X	X	X	X

a Visit 4 corresponds to the follow-up assessment conducted at Week 24, which is 12 weeks after completion of the 12-week treatment period, as stated in manuscript.

b Continuous monitoring throughout the study.

c Primary endpoint assessed at week 24.

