### Outcomes

2.9

The primary outcome of the trial will be the variation in the 6-minute walk test by week 24 as compared to baseline. The assessment of 6MWT will be performed in accordance with standardized procedures. The test will be conducted in a 30-meter corridor, and standardized instructions and encouragement will be provided to all participants. To ensure patient safety and consistency, predefined stopping criteria including intolerable dyspnea, chest pain, dizziness, or any other symptoms indicating potential risk, as judged by the assessor, will also be applied. The use of walking aids or supplemental oxygen will be permitted if clinically necessary, and the use will be recorded to minimize variability. Moreover, all outcome assessors will remain blinded to treatment allocation throughout the study to reduce measurement bias. The same assessor will evaluate a given participant across study visits to reduce inter-rater variability. All assessors will receive standardized training prior to study initiation. The 6MWT will be performed 1–2 h after routine medication administration to minimize variability. Duplicate tests will not be performed unless clinically indicated.

The secondary outcomes will include: (1) major adverse cardiovascular events (MACE, including cardiac death, non-fatal myocardial infarction, and rehospitalization due to HF) at 3 and 6 months. All major adverse cardiovascular events and heart failure-related rehospitalizations will be reviewed and adjudicated by an independent committee blinded to treatment allocation; (2) BNP levels at week 24 compared with baseline; (3) NYHA class functional classification at week 24 compared with baseline; (4) quality of life score of the Kansas City Cardiomyopathy Questionnaire at week 24 compared with baseline.

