### Statistical analysis

2.15

All statistical analyses will be conducted on both the intention-to-treat (ITT) and per-protocol (PP) populations. The ITT population will include all randomized participants, while the PP population will consist of participants with at least 80% adherence to the protocol. Continuous variables following a normal distribution will be presented as means ± standard deviations (SD) with 95% confidence intervals (CI), and non-normally distributed variables will be reported as medians with interquartile ranges (IQR) and analyzed using non-parametric methods. Between-group comparisons for normally distributed continuous variables will use the independent samples t-test, and for non-normal distributions, the Wilcoxon rank-sum test. Within-group comparisons will employ paired t-tests or Wilcoxon signed-rank tests as appropriate. Categorical variables will be summarized as counts and percentages, with between-group comparisons using the Chi-square or Fisher's exact test, and within-group comparisons using the McNemar test. Baseline characteristics will be reported descriptively without significance testing to assess comparability between groups. Differences in background treatment between groups will be summarized descriptively and adjusted for in the statistical analysis to reduce potential confounding.

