The primary outcome (6-minute walk test) will be analyzed using analysis of covariance (ANCOVA) with baseline values and key covariates (age, sex) as covariates to adjust for potential confounding. Secondary outcomes, due to their diverse nature, will be analyzed using appropriate methods: continuous variables with t-test or Wilcoxon test, categorical variables with Chi-square or Fisher's exact test, and repeated measures or longitudinal data using linear mixed-effects models. To control for multiple comparisons among secondary outcomes, the false discovery rate (FDR) adjustment using the Benjamini-Hochberg method will be applied, and a hierarchical structure will be applied with the primary outcome taking precedence over secondary and exploratory outcomes. The primary analysis will be conducted according to the intention-to-treat (ITT) principle, including all randomized participants. If the proportion of missing 6MWT data is 5% or greater, missing data for the 6MWT will be handled using multiple imputation under the missing-at-random assumption. The imputation model will include baseline 6MWT value, age, sex, and treatment group as predictors. Imputation will be performed using a single model based on all available data without separating treatment arm. In addition, reasons for missing data will also be recorded, categorized, and summarized descriptively, and will be compared between groups. Prespecified subgroup analyses will be conducted based on heart failure phenotype, defined by left ventricular ejection fraction (LVEF ≥50% vs. <50%), and by sex. These subgroup analyses will be considered exploratory. Sensitivity analyses will be performed, including per-protocol analyses and complete-case analyses, to assess the robustness of the results. Deaths occurring before the final assessment will be handled in sensitivity analyses using a worst-case approach by assigning a value of zero for the 6MWT, representing the worst functional outcome. Adverse events will be summarized in tables and compared between groups using descriptive statistics. All analyses will be performed using SAS software version 9.4, and two-tailed *P*-values < 0.05 will be considered statistically significant. A detailed statistical analysis plan will be finalized prior to database lock to ensure prespecified analysis procedures.

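### The protocol's rule for categorical secondary outcomes (chi-square or Fisher) by elimination covers NYHA class at week 24, where it is valid but discards class order and entry class and so loses power.

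*Protocol article*

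**What the plan says.** Section 2.9 (Outcomes) lists among the secondary outcomes "NYHA class functional classification at week 24 compared with baseline". Section 2.3 admits patients with "NYHA classification of II to III", so there are two classes at entry, while classes I to IV are possible at week 24. Table 1 schedules NYHA at all five visits.

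Section 2.15 (Statistical analysis) assigns tests by type of variable:

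- General rule for categorical variables: "with between-group comparisons using the Chi-square or Fisher's exact test", and "within-group comparisons using the McNemar test".
- Rule for secondary outcomes: "Secondary outcomes, due to their diverse nature, will be analyzed using appropriate methods". The list that follows includes "categorical variables with Chi-square or Fisher's exact test" and "repeated measures or longitudinal data using linear mixed-effects models".

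Adjustment for the baseline value is stated only for the primary outcome, the 6MWT, which is analysed by ANCOVA with age and sex as further covariates. No method for ordered categories is named, and NYHA does not appear in any of the test rules.

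**The concern.** NYHA class is ordered, and the protocol defines the outcome relative to baseline. Chi-square and Fisher's exact test treat the classes as unordered labels. Run on week-24 class, they also ignore the entry class, which is likely to be a strong predictor of the class at week 24. Randomisation is stratified by sex and age and not by NYHA class, so a chance imbalance in entry class would go uncorrected.

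The cost is lower power to detect a general shift towards better classes. There is also no single estimate, such as a common odds ratio, to report beside the p-value. The general McNemar sentence adds a smaller problem: that test is defined for a paired two-by-two table, and NYHA class has up to four levels.

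**Working it through.** **1. Which rule reaches NYHA.** The secondary outcomes are MACE, BNP, NYHA class and KCCQ score. BNP and KCCQ are continuous. MACE is an event outcome with two categories and no order to lose. NYHA is the only one with several ordered categories, so the chi-square/Fisher rule reaches it by elimination. The other listed route is the linear mixed model, which would treat the classes as equally spaced numbers.

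**2. Number of patients.** The protocol assumes a difference of 50 m, an SD of 72 m, two-sided α = 0.05 and 90% power. The normal approximation gives 2 × (1.960 + 1.282)² × 72² / 50² = 43.6, so 44 per arm. The t-test version gives 44.6, so 45. With 10% dropout, 45 / 0.90 = 50 per arm. The stated figures reproduce, and 45 evaluable patients per arm are used below. No power is stated for NYHA.

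**3. Order is not used.** Take an illustrative table for classes I to IV: control 5/20/17/3 and active 12/22/9/2.

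- Chi-square: the column totals are 17, 42, 26 and 5, so the expected counts per arm are 8.5, 21, 13 and 2.5. Then χ² = 2 × (3.5²/8.5 + 1²/21 + 4²/13 + 0.5²/2.5) = 5.64 on 3 df, p = 0.131. Scrambling the order of the classes gives the same p.
- Rank-sum: the mid-ranks are 9, 38.5, 72.5 and 88. The control rank sum is 2311.5 against 45 × 91/2 = 2047.5 expected. The tie-corrected SD is 115.4, so z = 264/115.4 = 2.29, p = 0.022.

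**4. Power, order only.** The week-24 control distribution is an assumption, because the documents give none. The effect is a common odds ratio (OR) for a better class, with 45 per arm.

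| Assumed control distribution | OR | Chi-square | Rank-sum | Loss (points) |
|---|---|---|---|---|
| I–IV 15/50/30/5% | 2.0 | 25% | 41% | 16 |
| | 2.5 | 44% | 62% | 18 |
| | 3.0 | 60% | 78% | 18 |
| Class IV empty, 15/50/35% | 2.0 | 32% | 40% | 8 |
| | 2.5 | 50% | 61% | 11 |
| | 3.0 | 67% | 76% | 9 |

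**5. Power, order and entry class.** Two further assumed sets of week-24 control distributions were used, each depending on entry class:

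- Set A: 20/70/9/1% after entry in class II, and 4/36/55/5% after entry in class III.
- Set B: 30/55/13/2% and 10/40/42/8%.

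Class III made up 30% or 50% of entrants. There were 3,000 simulated trials per scenario, and the stratified test is van Elteren's.

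| OR | Chi-square | Rank-sum | Rank test stratified by entry class |
|---|---|---|---|
| 2.0 | 16–22% | 28–37% | 34–41% |
| 2.5 | 29–38% | 45–56% | 56–63% |
| 3.0 | 42–53% | 61–70% | 73–77% |

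Within scenarios, the loss against the rank-sum test runs from 11 points (16.1% v 27.5%) to 19 points (51.1% v 70.0%). Stratifying by entry class adds a further 4 to 13 points. The total loss runs from 18 points (20.9% v 38.7%) to 31 points (42.2% v 73.4%). With no effect, all three tests reject in 3.8% to 5.5% of trials.

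**6. McNemar.** The test has 1 df on a paired 2×2 table. For k classes the symmetry extension (Bowker) has k(k−1)/2 df, which is 6 for k = 4. The protocol states neither that extension nor a two-category version of NYHA.

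**The case against.** The strongest reply is that the protocol never says NYHA will be tested this way. It gives rules by type of variable, NYHA is recorded repeatedly so the longitudinal route is textually open, and a detailed SAP is announced. That limits how firmly the point can be put: the link is by elimination. It does not remove the point, because the categorical rule for secondary outcomes is already stated and no listed route suits an ordered class.

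A reader might infer that the protocol prescribes McNemar for four-level NYHA class and that this analysis is therefore invalid. The text does not support that. McNemar stands only in the general rule for categorical variables and is not repeated for secondary outcomes. It would suit other paired items, such as ECG or urine results coded normal or abnormal, and it is valid for NYHA once dichotomised. It also uses baseline through the pairing, so the failure to use entry class belongs to the between-group test only.

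The protocol's wording would also allow an endpoint of improved versus not improved, and chi-square on that would use entry class. No such endpoint is stated, however, and it would still discard the size of the change.

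The power figures are fairly challenged too. They rest on assumed distributions, and the loss falls to 8–11 points if class IV is empty, which is plausible in stable class II–III patients. With class IV occupied, about 96% of simulated tables have an expected count below 5, where Fisher's test would usually be used; only Pearson's chi-square was simulated. Fisher's test ignores order equally, but its exact loss was not computed. The Benjamini-Hochberg adjustment applies to whichever test is chosen and is no argument against chi-square.

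**Conclusion.** The point holds as one of efficiency and interpretability. If the stated rule is applied to week-24 NYHA class, the test is valid and its type I error is controlled, but it leaves order and entry class unused and yields no common effect estimate. The loss is roughly 8 to 19 percentage points of power against a rank test and about 18 to 31 against a rank test stratified by entry class. These figures assume 45 evaluable patients per arm, a common odds ratio of 2 to 3, and NYHA distributions that the documents do not supply. The direction was the same in every scenario; the size is illustrative and is not a forecast for this trial.

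The weight is moderate to low. NYHA is one of four secondary outcomes, and section 2.14 powers the trial only for the 6MWT. It is still worth changing, because a better analysis of data already scheduled for collection is available at almost no cost.

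**What to change.** Name NYHA in section 2.15 and in the SAP, and choose one between-group analysis of week-24 class:

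- a proportional-odds model with treatment, baseline NYHA class, age and sex (the last two as for the 6MWT), reporting the common odds ratio with its 95% CI; or
- a CMH row-mean-score or van Elteren test stratified by baseline class.

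The model gives an effect estimate but needs the proportional-odds assumption. The stratified rank test avoids that assumption.

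State that the general McNemar rule does not apply to multi-level NYHA class. Drop it for NYHA, or restrict it to a prespecified two-category version, as a descriptive within-group summary only.

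The cost is a few sentences. No further data or patients are needed, and these are standard procedures in the SAS software already named.

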### Randomization and blinding

2.6

This is a single-center study conducted at Hangzhou Hospital of TCM. Randomization will be performed by an independent statistician who is not involved in patient recruitment, intervention, or outcome assessment. The randomization sequence will be generated using SAS software version 9.4, with a 1:1 allocation ratio, stratified by sex, and age, utilizing random block sizes of six. Allocation concealment will be ensured using a centralized system, and researchers, participants, and data administrators and statisticians will be unaware of the randomization and treatment allocations. To ensure the blinding of participants and investigators, the placebo is identical to FJHQG in appearance, color, taste, packaging. Emergency unblinding will only be performed when necessary for patient safety and must be approved by principal investigator, and all such events will be documented.

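### BNP and KCCQ fall under two competing analysis rules, and neither states the baseline adjustment that the 6-minute walk test receives

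*Protocol article*

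**What the plan says.** Section 2.9 defines the two continuous secondary outcomes relative to baseline: "BNP levels at week 24 compared with baseline" and "quality of life score of the Kansas City Cardiomyopathy Questionnaire at week 24 compared with baseline". Table 1 schedules both at screening, at a day-6 visit and at weeks 4, 12 and 24.

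Section 2.15 treats the outcomes differently:

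- The 6-minute walk test gets ANCOVA "with baseline values and key covariates (age, sex) as covariates to adjust for potential confounding".
- Continuous secondary outcomes get "continuous variables with t-test or Wilcoxon test". The general rule earlier in the section makes the choice depend on the data: "Between-group comparisons for normally distributed continuous variables will use the independent samples t-test, and for non-normal distributions, the Wilcoxon rank-sum test".
- The same sentence on secondary outcomes adds "repeated measures or longitudinal data using linear mixed-effects models", without naming the outcomes it covers or the covariates.
- For all analyses it promises: "Differences in background treatment between groups will be summarized descriptively and adjusted for in the statistical analysis to reduce potential confounding".

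Section 2.6 says that randomisation is "stratified by sex, and age, utilizing random block sizes of six".

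**The concern.** BNP and KCCQ are continuous variables, and they are also longitudinal data, so both clauses of one sentence apply to them. The article does not say which governs. Three tests are therefore open for each outcome (t-test, rank-sum, mixed model), while the Benjamini-Hochberg procedure needs one p-value per outcome. The rules would also use different patients. A week-24 t-test or rank-sum test drops anyone without a week-24 value, because multiple imputation is stated only for the walk test. A mixed model keeps those patients' earlier visits.

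The first clause also cannot deliver what the rest of the section sets out. A two-sample t-test or rank-sum test, as named, carries no covariates, so it cannot adjust for the outcome's baseline value, for the stratification factors or for background treatment. If BNP is judged non-normal, the result would be a rank test without an adjusted effect estimate. At stake are precision and prespecification for two secondary outcomes.

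**Working it through.** **The plan's own figure.** Section 2.14 gives a difference of 50 m, SD 72 m, two-sided α = 0.05 and power 90% for the walk test. The normal approximation gives 44 per arm. The t-based solution is 44.56, so 45, as stated. With 10% dropout, 45/0.9 = 50 per arm. The sample size reproduces, and it has no counterpart for BNP or KCCQ.

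**Which rule applies?**

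| Rule in Section 2.15 | Fits BNP and KCCQ? | Baseline as covariate? | Age, sex, background treatment? |
|---|---|---|---|
| t-test or Wilcoxon, by distribution | Yes, continuous | Not possible | Not possible |
| Linear mixed model | Yes, five scheduled measurements | Not stated | Not stated |
| ANCOVA | Stated for the walk test only | Yes | Age and sex |

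**Precision under the t-test branch.** The Section 2.9 definitions most naturally mean change from baseline. Let ρ be the correlation between baseline and week 24, with equal variance σ² at both times.

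- Per-patient variance of change: 2σ²(1−ρ).
- Residual variance under ANCOVA: σ²(1−ρ²). This ignores the small cost of estimating the slope.
- Ratio: (1−ρ)(1+ρ) / [2(1−ρ)] = (1+ρ)/2.

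The article gives no ρ for BNP or KCCQ, so a range of 0.3 to 0.8 is assumed. To express the ratio as power, take a true difference of 0.591 raw SDs with 45 per arm (normal approximation). That difference comes from (1.960 + 0.842) × √(2/45), which gives 80% power when the per-patient variance is σ².

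| ρ (assumed) | ANCOVA variance / change-score variance | Power, t-test on change | Power, ANCOVA |
|---|---|---|---|
| 0.3 | (1+0.3)/2 = 0.65 | 66% | 84% |
| 0.5 | (1+0.5)/2 = 0.75 | 80% | 90% |
| 0.7 | (1+0.7)/2 = 0.85 | 95% | 97.5% |
| 0.8 | (1+0.8)/2 = 0.90 | 99% | 99.7% |

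At ρ = 0.5, ANCOVA would match the change-score t-test with 0.75 × 45 = 33.75, or about 34, patients per arm. The ratio is below 1 for every ρ strictly between 0 and 1.

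**Limits.** The formula compares ANCOVA with a t-test and does not apply to the Wilcoxon branch, for which no loss is computed. It also says nothing about the mixed-model branch, which could match or improve on ANCOVA if it included baseline.

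**The case against.** Several stronger readings are tempting, and the article does not support them.

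- A reader might infer that the baseline values are thrown away. They are not: both outcomes are defined relative to baseline, and a change score uses the baseline value, only less efficiently than ANCOVA. The larger losses that follow from comparing week-24 values alone (variance ratio 1−ρ²) belong to an analysis that the article does not describe.
- A reader might take the t-test or Wilcoxon test as the settled method. The mixed-model clause may already be meant for BNP and KCCQ. The loss above is therefore conditional on the first clause being used.
- A reader might infer bias or excess false positives. An unadjusted comparison of randomised groups is unbiased, and ignoring stratification factors generally makes standard errors too large, which is conservative. A change score also takes partial account of chance baseline imbalance.
- A reader might infer freedom to pick a favourable result. Section 2.6 keeps statisticians unaware of allocation, and Section 2.15 promises a full analysis plan before database lock. A normality-based switch under blinding is poor practice, but it is not selection on the treatment effect.

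It can also be argued that covariates and transformations for secondary models belong in the analysis plan, and that these outcomes rank below the primary in a study whose limitations section calls the design exploratory. That limits the weight of the point but does not remove it. The article does not stay silent: it names tests that cannot meet its own adjustment statement, and it names a second method for the same outcomes.

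**Conclusion.** The point holds as one of precision and prespecification for BNP and KCCQ. The article leaves two rules for each outcome and states no baseline adjustment under either. The t-test or Wilcoxon rule also conflicts with the promised adjustment for background treatment. If a t-test on change were used, its variance would exceed what ANCOVA gives: the reduction available is 35% at ρ = 0.3, 25% at 0.5, 15% at 0.7 and 10% at 0.8. These figures rest on an assumed ρ, equal variances and the change-score reading. The treatment comparison stays unbiased, and the primary analysis and the 100-patient sample size do not change. It should be corrected, and it does not threaten the trial's main conclusion.

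**What to change.** Name one analysis for each outcome in Section 2.15 and carry it into the analysis plan before database lock:

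- **Model.** Use ANCOVA, or a repeated-measures mixed model, on log-transformed BNP and on the KCCQ score, with the outcome's baseline value, age and sex as covariates. The log scale assumes that BNP is right-skewed. This is plausible because entry sets a lower limit of 35 pg/mL and no upper limit, but the article does not show it.
- **Baseline.** Define it as the pre-treatment screening value. Table 1 puts its baseline label on the day-6 visit, which Section 2.8 places after the start of treatment.
- **Inference.** Let the week-24 contrast supply the single p-value per outcome for the Benjamini-Hochberg procedure.
- **Reporting.** Give a ratio of geometric means for BNP and an adjusted mean difference for KCCQ, each with a confidence interval.
- **Switch.** Drop the normality-based choice of test for these outcomes. A Wilcoxon test may stay as a sensitivity analysis.
- **Background treatment.** Reconcile the promised adjustment with the chosen model.

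The cost is wording only: the data are already scheduled, and the model is the primary one or a close extension of it.

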**Methods:**

This trial is a randomized, double-blind, placebo-controlled study that recruits 100 patients with HF. Participants will be randomly assigned into the intervention and control groups (*n* = 50 for each group). For a duration of 12 weeks, FJHQG will be administered to the intervention group, and the control group will receive standard therapy plus placebo. The primary outcome of the trial is the changes of six-minute walk test at week 24. Secondary outcomes include BNP levels, NYHA classification, major adverse cardiovascular events (MACE), and KCCQ quality of life scales. Other exploratory assessments at the beginning and after a 12-week period will include fluid balance, symptom score scales, echocardiograms, diuretic consumption, and biochemical indices. Monitoring of MACE will continue until 12 weeks after drug discontinuation.

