### Sample size calculation

2.14

Patients will be randomized in a 1:1 ratio to receive either FJHQG or placebo. Previous studies in HF suggested that improvements of approximately 30 meters in the 6MWT is clinically meaningful. According to our previous clinical observation, assuming FJHQG demonstrates an improvement of 50 meters in 6MWT compared with placebo and a standard deviation of 72 meters among two groups, a two-sided significance level of *α* = 0.05, and a statistical power of 90%. The results indicate that at least 45 patients will be needed per group. Considering an anticipated dropout rate of 10%, a total of 100 patients will be enrolled, with 50 allocated to the intervention group and 50 to the placebo group. The study is powered for the primary functional endpoint and is not designed to detect differences in clinical events.

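### None of the listed methods for secondary outcomes allows for incomplete MACE follow-up; a time-to-first-event analysis at weeks 12 and 24 would be a minor, cheap improvement

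*Protocol article*

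**What the plan says.** Section 2.9 lists MACE first among the secondary outcomes: "including cardiac death, non-fatal myocardial infarction, and rehospitalization due to HF) at 3 and 6 months". The other secondary outcomes there are set at week 24. An independent blinded committee adjudicates the events.

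The abstract fixes the end of observation: "Monitoring of MACE will continue until 12 weeks after drug discontinuation". Section 2.8 places the last visit at the same point: "Follow-up assessments will be conducted at Week 12 ± 7 days post-discontinuation of treatment (24W ± 7d) (visit 4"). Table 1, footnote b, says of MACE: "Continuous monitoring throughout the study".

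Section 2.15 says that secondary outcomes get methods suited to their type and then names them. Continuous outcomes get a t-test or Wilcoxon test. The next entry is "categorical variables with Chi-square", with Fisher's exact test as the alternative. Longitudinal data get linear mixed-effects models. Benjamini-Hochberg adjustment covers the secondary outcomes. The analyses are to be run on all randomised participants and on the per-protocol set. The only missing-data rule is multiple imputation for the 6MWT.

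Section 2.14 enlarges the sample for loss ("Considering an anticipated dropout rate of 10" per cent) and states that the trial is not designed to detect differences in clinical events. Section 2.15 announces a detailed SAP before database lock.

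**The concern.** Of the listed methods, only the comparison of proportions fits an event outcome such as MACE. Applied to all randomised patients, that comparison needs a yes or no for everyone. A patient who leaves at week 6 without an event has neither. The analyst must count that patient as event-free, which biases the risk downwards, or leave the patient out, which biases it upwards because early leavers who already had an event stay in. If loss differs between arms, either choice produces a difference that is not a treatment effect.

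Continuous monitoring and adjudication should make event dates obtainable, and the comparison of proportions discards them. The time points are also labelled in months, while observation ends at a visit defined in weeks. MACE is the first-listed secondary outcome and belongs to the FDR-adjusted family, so its p-value will be reported and will enter that adjustment.

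**Working it through.** **Plan's own figure.** The protocol states no MACE rate, event count or MACE power. Its one sample-size figure reproduces. With a difference of 50 m, SD 72 m, two-sided alpha 0.05 and power 90%, n per arm = 2 × (1.960 + 1.282)² × 72² / 50² = 43.6, so 44 by the normal approximation. The t-test version gives 44.56, so 45, as stated. Then 45 / 0.90 = 50 per arm, 100 in total. The 10% allowance implies about 10 leavers.

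**Time points.** Week 24 is day 24 × 7 = 168, with a window of day 161 to 175. Six calendar months are 365.25 / 2 = 182.6 days, so the last visit falls about 15 days short (about 8 to 22 over the window). Week 12 is day 84, against 365.25 / 4 = 91.3 days for three months.

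**Bias of a crude proportion.** Assumptions: 24-week MACE risk r of 10% or 20%, constant hazard, and a fraction d leaving evenly over 24 weeks. With L = -ln(1 - r), a leaver's average risk while still observed is m = 1 - r / L.

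- Leavers counted as event-free: (1 - d) × r + d × m.
- Leavers without an event excluded: the same numerator divided by 1 - d × (1 - m).

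| r | d | m | Counted event-free | Excluded |
|---|---|---|---|---|
| 0.10 | 0.10 | 0.0509 | 0.0951 (-4.9%) | 0.1051 (+5.1%) |
| 0.20 | 0.10 | 0.1037 | 0.1904 (-4.8%) | 0.2091 (+4.6%) |
| 0.10 | 0.15 | 0.0509 | 0.0926 (-7.4%) | 0.1080 (+8.0%) |
| 0.20 | 0.15 | 0.1037 | 0.1856 (-7.2%) | 0.2144 (+7.2%) |

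At r = 0.10 and d = 0.10 the error per arm is 50 × (0.10 - 0.0951), about a quarter of one event.

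**Unequal dropout.** Both arms have the same true risk, leavers count as event-free, and dropout times are exponential. The observed proportion is L / (L + M) × (1 - exp(-(L + M))), with M = -ln(1 - d).

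| Assumed 6-month risk | 24-week risk | False difference, 5% vs 15% | False difference, 0% vs 20% |
|---|---|---|---|
| 5% | 4.6% | 0.2 points | 0.5 points |
| 10% | 9.2% | 0.5 points | 0.9 points |
| 20% | 18.6% | 0.9 points | 1.9 points |
| 30% | 28.0% | 1.4 points | 2.8 points |

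At 24-week risks of exactly 10% and 20%, the 5% vs 15% case gives 0.5 and 1.0 points. The 1.4-point figure belongs to a risk near 28%.

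**Power.** Chi-square uses 50 per arm with complete follow-up. Log-rank uses the Schoenfeld formula, Φ(√(D/4) × |ln HR| - 1.96), with the D events expected under 10% dropout.

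| Assumed 24-week risks | D | Chi-square | Log-rank |
|---|---|---|---|
| 10% vs 5% | 7.1 | 16% | 16% |
| 20% vs 10% | 14.3 | 29% | 29% |
| 30% vs 15% | 21.4 | 43% | 44% |

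A time-to-event analysis is therefore not justified by power. Its merit is that it uses each patient's observed time.

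**The case against.** The strongest reply is that no sentence assigns a test to MACE. Section 2.15 gives defaults by type of variable, speaks of appropriate methods and defers detail to an SAP that is not shown. That stands in part. A reader might infer that the protocol fixes MACE as a yes/no outcome tested by chi-square. The text does not say so, and it allows Fisher's exact test. What remains is that the protocol does list its methods, and only this one fits.

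A reader might also infer that censoring is ignored. The protocol is silent on how incomplete MACE follow-up is counted, and silence is not a rule. The 10% is an allowance for the 6MWT sample size, not a stated loss of event follow-up. Patients who miss a walk test can still be reached through the telephone and WeChat contact in section 2.8.

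A third tempting reading is that the 6-month risk is never observed. Monitoring ends at week 24 and the other secondary outcomes are labelled that way, so six months is most naturally a loose name for that visit. The mismatch is one of labelling.

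Finally, Kaplan-Meier and log-rank methods assume that leaving is unrelated to event risk. If patients leave because they deteriorate, the proposed analysis is biased too. Censoring non-cardiac death would also overstate cumulative MACE risk. Both points are right and shape the remedy. With few events over one short window, Fisher's exact test is defensible and is worth keeping as support.

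**Conclusion.** The point holds as a minor improvement. The listed methods leave only chi-square or Fisher's exact test for MACE, and neither accommodates patients who leave early without an event. At assumed 24-week risks of 10% to 20% with even 10% dropout, the error is about 5% in relative terms. It goes in the same direction in both arms if loss is equal, so it largely cancels in the comparison. Over the wider range of assumed risks, unequal loss of 5% against 15% yields a false difference of 0.2 to 1.4 points, and even 0% against 20% stays below 3 points.

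These sizes rest on assumed event risks, constant hazards and dropout unrelated to outcome. Informative dropout could make the error larger, and the documents give no basis for quantifying it. No conclusion on the 6MWT depends on this, and the protocol disclaims power for clinical events.

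**What to change.** - **Section 2.9:** replace the 3- and 6-month time points for MACE with week 12 and week 24, matching the end of monitoring.
- **Section 2.15 and the SAP:** define MACE as time from randomisation to first adjudicated event, censored at last contact or week 24. Report cumulative risk with 95% CI at weeks 12 and 24, and enter one log-rank test into the FDR family.
- **Non-cardiac death:** treat it as a competing event and estimate risk by cumulative incidence. The log-rank test then compares the rate of MACE among patients still at risk.
- **Supportive analysis:** keep counts by arm with Fisher's exact test, and state how early leavers are counted in it.
- **Dropout:** report reasons for leaving by arm, because censoring at last contact still assumes that leaving is unrelated to event risk.

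The cost is wording in two sections and the SAP before database lock. No new data should be needed, provided that event and last-contact dates are recorded. The downside is imprecision: with few events the risk estimates will have wide intervals, and a hazard ratio may not be worth reporting.
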